##### Aerobic

To assess the effect of a single bout of aerobic exercise on executive control, we use an exercise stimulus based on the American College of Sports Medicine guidelines for improving aerobic capacity, which consists of 21 min of exercise on a treadmill at 70–75% of the individual’s maximum heart rate. Participants engage in a 1-min warmup and a 1-min cooldown, with the majority of time (i.e., 19 min) spent exercising at 70–75% of HRmax. Participants’ exercise on a motor-driven treadmill at a constant speed during the 19-min period. Based on fitness level and participant ability, they may walk or run. Once the desired speed is set, the incline is adjusted to reach the desired intensity.

##### Trier Social Stress Test for children (active control)

Children participate in a modified laboratory stress protocol based on the TSST for children [31]. The TSST for children consists of a speech task in which children talk about themselves and complete a mental arithmetic task in front of a camera (which does not record the session, but is there simply to induce stress) and three neutral observers. Specifically, participants are asked to imagine that they are in a new class with 20 other students, and that their teacher has asked them to stand in front of the class and introduce themselves. Children are instructed to speak for 6 min about themselves, their personality, and why they believe that they would be liked by their classmates. In addition, they are asked to discuss at least one good and one bad aspect of themselves. The mental arithmetic task entails asking children to serially subtract the number 5 from a larger number as quickly as possible for 4 min. The TSST for children lasts approximately 14 min. Although the TSST for children is shorter in duration than the exercise task, prior research has shown that it successfully elevates sAA and CORT levels [32].

##### Rest (passive control)

Participants sit in a comfortable chair, placed in the same room as the motor-driven treadmill, for 20 min. Children are asked to sit quietly or read a book of their choosing (excluding schoolwork). They are instructed to minimize conversation.

#### Cognitive tasks

##### Go-NoGo task

In the Go condition, participants are asked to respond to an infrequent target stimulus (cartoon drawing of a lion), occurring on 20% of the trials, and not to respond to the frequent stimuli (cartoon drawing of a tiger), occurring on 80% of the trials. Next, participants complete the NoGo condition, wherein the rules are reversed. Participants respond to the frequent non-target stimuli, while not responding to the rare, target stimuli. This fixed task order is used to build a prepotent response to respond to the rare stimuli. Participants complete one block of 250 trials for each condition (Go, NoGo). Stimuli appear for 200 ms and a black background with a variables inter-stimulus interval (ISI) of about 1500 ms.

##### Flanker task

A modified flanker task consists of five 3-cm-tall white arrows focally presented on a black background of a computer screen. Participants are instructed to respond using a response pad as quickly and accurately as possible with a thumb press according to the directionality of the centrally presented target arrow amid either congruent (pointing in the same direction) or incongruent (pointing in the opposite direction) flanking arrows. Congruency and directionality are equiprobable. Participants complete one block of 156 trials, with stimuli presented for 150 ms with a variable ISI of (1300, 1500, and 1700 ms).

#### Neuroelectric assessment: electroencephalogram (EEG)

One of the primary aims of the SNEACY study is to examine the acute changes that occur in brain function following exercise intervention. Accordingly, on sessions 2, 3, and 4, children are fit with an EEG cap in order to measure brain activity before and after intervention. EEG activity is measured from 64 electrodes and 4 integrated bipolar leads for vertical and horizontal EOG (VEOG, HEOG), arranged according to the international 10–10 system using a Neuroscan Quik-cap (Compumedics, Inc., Charlotte, NC). EEG data is collected while cognitive tasks are completed.

#### Academic achievement testing

##### Wide Range Achievement Test 4 (WRAT4)

Participants complete the WRAT-4 assessment tests for reading (the number of words pronounced correctly) and mathematics (the number of mathematical computations completed correctly). The WRAT-4 is a commercially available paper and pencil based academic achievement assessment that has been age normed. The WRAT allows for repeated administration through the use of two equivalent forms. Administration of the WRAT-4 is conducted by trained experimenters with the duration of the assessment lasting ~ 30 min. Each child completes one version of the WRAT-4 following their rest session, and one version of the WRAT-4 following either their aerobic or TSST session, since only two versions of the task exist.

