## Material and design

### Summary of aims

The objective of the SNEACY study is to test several aims: (1) Investigate basic laboratory and applied scholastic performance aspects of brain function, cognition, and academic achievement following aerobic exercise compared to active (i.e., Trier Social Stress Test for Children (TSST); a commonly used psychosocial stressor) and passive (i.e., seated rest) control conditions; and (2) Investigate phasic changes in SNS activation (as indicated by sAA) as a potential mechanism for the transient beneficial effect of exercise on brain function, cognition, and academic achievement. Phasic activation refers to brief, rapid changes in the SNS [17] in response to salient or task-relevant information in the stimulus environment [18]. Phasic sAA has been shown to be related with attention, memory, and various academic outcomes [16, 18–22]. SNEACY is a randomized crossover trial with three acute interventions: 20 min of moderate intensity treadmill exercise, 20 min of seated rest, and a 14-min TSST for Children. The TSST and seated rest interventions serve as active and passive control conditions, respectively, for the experimental intervention involving moderate intensity exercise. As a result of this design, changes observed in the aerobic exercise intervention can be attributed to the exercise component of the intervention rather than to other, potentially confounding factors, such as expectancy effects, stress, or elevated heart rate. The study will enroll and randomize 103 typically developing, 9–10-year-old children. We hypothesize that exercise-induced phasic increases in SNS activity, indicated by sAA levels, will mediate the effect of a single bout of exercise on brain function (i.e., P3 amplitude and latency), cognition (i.e., executive control), and standardized achievement test performance (i.e., mathematics, reading). To further explore a relation between exercise-induced change in sAA with brain and cognition, baseline and stress-induced (i.e., exercise, TSST) change in cortisol will be investigated as a potential factor in the analytical model. All participants provide written assent/consent (and legal guardians provide written informed consent) by a trained research technician in accordance with the Institutional Review Board of Northeastern University. The study was designed in accordance with the SPIRIT statement, details are provided in Fig. 1.

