### Primary outcome

The primary outcomes are changes in cognitive performance following each of the three acute interventions. Specifically, we predict that exercise-induced phasic increases in SNS activity, indicated by sAA levels, will mediate the effect of a single bout of exercise on brain function (i.e., P3 amplitude and latency), cognition (i.e., executive control), and standardized achievement test performance (i.e., mathematics, reading).

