#### Days 2–4 procedure

At intervention visits (days 2, 3, and 4), the participant engages in the same protocol each day, with the sole exception of a different intervention each day. At the start of each visit, children are outfitted with a heart rate monitor to measure the intensity of the intervention. Upon entering the laboratory, children are asked to sit quietly for 10 min to allow their heart rate to return to baseline levels, after which they provide the first saliva sample by drooling into a tube. Participants are then fitted with an EEG cap. Next, they complete cognitive tasks on a computer while EEG data is simultaneously collected. Then, the child completes one intervention at each visit: (1) aerobic exercise, (2) quiet resting, or (3) the TSST. Upon completion of the intervention, participants provide another saliva sample. Participants then complete the same cognitive tasks again while EEG data is simultaneously collected. Participants will provide another saliva sample, and then they will complete an academic achievement test. At the end of the visit, the final saliva sample is collected. Visits 2–4 last approximately 2.5 h each. At the conclusion of study participation, no further ancillary or post-trial care was offered.

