### Power and analytic strategy

A traditional power analysis was conducted to estimate the appropriate sample size necessary for detecting a mediating effect of sAA levels on the relationship between a single bout of aerobic exercise and acute changes in cognition given the inclusion of potentially confounding variables (e.g., age, sex, BMI, IQ, SES) based on a one-sided alpha of .01 to correct for multiple outcomes and a power of 0.8. For the total effect of exercise on the ERP and cognitive outcomes, an effect size was calculated from the results reported in Hillman et al. [9], which observed increased P3 amplitude, task performance, and scholastic achievement following acute exercise relative to rest in a sample of preadolescent children resulting in a moderate-to-large effect size (Cohen’s *d* = 0.79). Therefore, assuming a medium size of Cohen’s *f*2 = 0.15 for the total effect and 8 predictors (including exercise condition, subject ID, and covariates) in the regression model, power analysis indicate that a sample size of 82 participants will provide adequate power to detect the effects of a single bout of exercise on neuroelectric function and behavioral performance. For the mediation analysis, medium effect sizes [33] were assumed for both the direct effect of exercise on sAA levels (path a: coefficient = a) and the direct effect of sAA level on the outcomes controlling for treatment condition (path b: coefficient = b). Corresponding to Cohen’s [34] criteria for medium (13% of the variance) effect size, the values of a and b were set at 0.39. Applying the Sobel [35] first-order test, the indirect effect or the mediated effect of exercise on outcomes through sAA was indicated by the product of a and b and was tested. Empirical power results [36] showed that a sample size of *N* = 103 per study was required to detect the presence of mediation. Accordingly, we aim to recruit *N* = 120 to account for attrition.

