We will investigate whether the effect of the experimental conditions (*x*) on brain function, cognition, or academic achievement (distal *y* outcomes) is mediated by sAA and CORT baseline levels (*i*) and sAA change (*s*) using a path modeling framework (Mplus v8) and conventional model-to-data fit indices [37]. Each model will be adjusted for the set of potentially confounding variables (e.g., age, sex, BMI, IQ, SES). We will interpret significant direct effects on each outcome as supporting our hypotheses. We aim to incorporate the change process of sAA (*s*) and CORT (*s*) within the same model (allowing s and s to covary). We will utilize the most current and recommended practices [38, 39] for testing moderated mediation framework that leverages the stability of the entire sample for model estimation (causal structure); 5000 bootstrap draws will be run to collect the bias-corrected bootstrapped confidence intervals (95% CI) and significant indirect effects will be decomposed in Mplus output (identical to the Sobel test [35]). If mediation is found, subsequent tests of moderation will be conducted. To test the effect of the treatment condition (i.e., exercise, TSST-C, rest) on univariate continuous outcomes (brain function, cognition, academic achievement), three separate models will be tested using planned comparisons with imposed group invariance constraints. Group comparisons in sAA mean can be simultaneously compared (Is sAA larger in exercise compared to TSST-C and/or rest?), while also comparing benefits in the continuous outcomes regressed on sAA.

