## Discussion

The SNEACY study is a large, ongoing randomized crossover trial with a goal of investigating phasic changes in SNS activation (indicated by differential sAA and CORT trajectories) as a potential mechanism for the transient beneficial effect of moderate intensity exercise on brain function, cognition, and academic achievement in cognitively normal children. We predict that following the cessation of moderate intensity exercise performance on executive function tasks will improve, with enhanced neuroelectric functioning and that these improvements will be linked to changes in sAA. In addition, both sAA and cortisol are expected to increase in response to both exercise and the TSST-C in children. This is a well-designed and controlled study, with the exercise prescription individualized to each child reflecting their specific moderate intensity exercise. We further predict that academic performance will be greatest following exercise.

While this is a well-designed, detailed study, it is not without its limitations. The findings from this study will not allow us to determine whether different doses of exercise (i.e., duration, intensity, etc.) result in differences is neuroelectric profiles and cognition. However, we do expect to observe differences in performance based on an individual’s fitness and body composition. Our active control intervention is designed to increase psychosocial stress for the participants, and to increase their heart rate as a result. However, our passive control group is seated at quiet rest and prior research does not indicate cognitive benefits following seated rest [8–10]. In this sense, this is a well-controlled study with the inclusion of positive (TSST-C) and negative (seated rest) conditions. Finally, it would be impossible to measure all individual differences across our participants, which could influence their performance following interventions. There are several challenges that large-scale studies such as this one face. Primarily, ensuring accurate saliva measures from children may be a challenge, and relies on day of pre-intervention compliance from children and their parents. In addition, children must produce enough saliva in a set amount of time. Maintaining compliance and interest over a number of visits for children may be challenging as well.

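### Each child takes the WRAT-4 after rest and after only one of exercise or the TSST, so the single N = 103 and the own-control claim do not carry over to academic achievement

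*Protocol article*

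**What the plan says.** All places are in the protocol article.

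- **Wide Range Achievement Test 4 (WRAT4).** Each child takes one form after rest and "one version of the WRAT-4 following either their aerobic or TSST session, since only two versions of the task exist". The split between aerobic and TSST is not given.
- **Days 2–4 procedure.** At the intervention visits "the participant engages in the same protocol each day, with the sole exception of a different intervention each day". The common sequence includes the test: "Participants will provide another saliva sample, and then they will complete an academic achievement test". Table 2 likewise schedules academic testing in the shared Days 2–4 timeline, with no visit excepted.
- **Summary of aims.** Aim 1 covers "academic achievement following aerobic exercise compared to active" and passive control conditions.
- **Primary outcome.** The mediated outcomes include "standardized achievement test performance (i.e., mathematics, reading"), beside P3 and executive control.
- **Power and analytic strategy.** The calculation is "based on a one-sided alpha of .01 to correct for multiple outcomes and a power of 0.8". It arrives at 82 for the total effect and 103 for mediation, with recruitment of 120. The condition effect is to be tested on "univariate continuous outcomes (brain function, cognition, academic achievement), three separate models will be tested using planned comparisons".
- **Interventions.** Participants are described as their own controls.
- **Discussion.** "We further predict that academic performance will be greatest following exercise".

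**The concern.** Under the WRAT4 section no child has both a post-exercise and a post-TSST score. Two consequences follow for mathematics and reading. The exercise-rest comparison rests on a subset of the children, and the exercise-TSST comparison has no within-child pair at all. Yet academic achievement shares one sample size and one own-control description with outcomes measured at all three visits.

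This is a matter of design: no analysis plan can recover scores that are never collected. At stake is the reading of the academic result. If mediation or an exercise effect is not found for mathematics or reading, a reader relying on N = 103 would take it as adequately powered evidence of absence. The Discussion's prediction ranks exercise above both controls, and one of those comparisons is much less precise than the crossover label suggests.

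**Working it through.** **Inputs from the protocol article (Power and analytic strategy).** One-sided alpha .01; power 0.8; f² = 0.15 with 8 predictors; a = b = 0.39; Sobel first-order test; N = 82, 103 and 120. The analysis itself uses 95% confidence intervals, so two-sided .05 is shown as well. **Assumption:** the share of children tested after exercise, taken as 1/2 and varied from 1/3 to 2/3.

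**1. The plan's own figures.**
- Mediation: N = 2(z_α + z_β)²/0.39².
  - Two-sided .05: 2(1.960 + 0.842)²/0.1521 = 103.2, which matches 103.
  - One-sided .01: 2(2.326 + 0.842)²/0.1521 = 132, which does not.
- Total effect: one coefficient, noncentral t with noncentrality √(0.15N) and N − 9 degrees of freedom. N = 82 gives power 0.80 at two-sided .01 and 0.87 at one-sided .01, so 82 matches two-sided .01.

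The mismatch with the stated alpha is a separate problem. It matters here because part of any shortfall at one-sided .01 would exist even with complete data.

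**2. Exercise-rest academic pairs.** 103 × 1/3 = 34; 103 × 1/2 = 51.5; 103 × 2/3 = 69. With all 120 recruited and no attrition: 40, 60 and 80. All fall below both 82 and 103.

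**3. Total effect at f² = 0.15, one-sided .01 (formula in step 1).** N = 103: 0.94. N = 60: 0.72. N = 52: 0.65. Across the range of shares: 0.43 at 34 pairs, 0.79 at 69.

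**4. Mediation.** Sobel power = Φ(ab/√(a²/n_b + b²/n_a) − z_α), where n_a and n_b are the numbers of children informing paths a and b. For 103 pairs, the first term is 0.39 × √(103/2) = 2.80. With both paths on 51.5 it is 1.98. With path a on 103 and path b on 51.5 it is 2.29.

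| Data used | Two-sided .05 | One-sided .01 |
|---|---|---|
| 103 pairs | 0.80 | 0.68 |
| Path a on 103, path b on 51.5 | 0.63 | 0.48 |
| Both paths on 51.5 | 0.51 | 0.36 |

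At two-sided .05, over shares from 1/3 to 2/3, the range is 0.37 to 0.63 with both paths on the subset and 0.51 to 0.71 with path a on all 103.

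**5. Pooling path b.** I simulated difference scores with unit residual variances, N = 103, an even split, 20,000 replicates, and path b assumed equal for rest-aerobic and rest-TSST pairs.

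| Data used | Two-sided .05 | One-sided .01 |
|---|---|---|
| 103 exercise-rest pairs | 0.89 | 0.73 |
| Path a on all, path b pooled over both pair types | 0.89 | 0.72 |
| Path a on all, path b on exercise-rest pairs only | 0.63 | 0.40 |
| Both paths on the subset | 0.40 | 0.18 |

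Simulated and closed-form power differ because the Sobel statistic is not normal at these sizes. The ordering is the same.

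**6. Exercise versus TSST.** About 51.5 children per group, d = 0.5, one-sided .01: Φ(0.5√(51.5/2) − 2.326) = 0.58. Adjusting for the child's own rest score divides the first term by √(1 − r²). This gives 0.73, 0.89 and 0.97 for assumed correlations of 0.5, 0.7 and 0.8.

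**The case against.** The strongest reply is that the subset figures are a worst case the plan does not prescribe. Saliva is collected at every intervention visit, so path a keeps every child. Every child also has a WRAT-4 pair of one kind or the other, and the analysis section speaks of using the whole sample for estimation and of invariance constraints across groups. If path b is the same in both pair types, step 5 shows almost no loss. This stands, but on an assumption that the article does not state for this outcome.

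The simple exercise-rest contrast is also not hopeless. At one-sided .01, 52 pairs give power 0.88 for a paired effect of 0.5 SD of the difference, and above 0.99 for 0.79, the cited effect if read as a paired one. This stands too; the shortfall arises at the medium effects on which the plan chose its size. In addition, the 82 is worded for neuroelectric and behavioural outcomes, so it is the 103, given for outcomes in general, that most clearly claims to cover achievement.

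Three stronger readings are tempting and not supported:
- That power for mathematics and reading is simply far below 0.8. It depends on the effect, the contrast and how path b is estimated, and at one-sided .01 part of the gap remains with 103 pairs.
- That staff or visit order choose which session carries the test, so that the contrast is biased. The article is silent, and a condensed article may leave such allocation detail to the full protocol.
- That exactly half the children are affected. The split is not given.

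**Conclusion.** The point holds in bounded form. The WRAT4 section is the specific text and gives its reason, so I take it as governing; the visit procedure and Table 2 contradict it. If all three visits did carry the test, the power point would fall and only the contradiction would remain.

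Taken as written, the exercise-rest academic pair exists only in the children tested after exercise. Exercise versus TSST is between children for this outcome; the rest score can recover precision but does not make it a within-child comparison. The single N = 103 reflects neither fact.

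Under an even split, total-effect power at the plan's medium effect falls from 0.94 to about 0.65. Sobel power at two-sided .05 falls from 0.80 to between 0.51 and 0.63, unless path b is assumed common and pooled. No share from one third to two thirds reaches 0.80 for mediation without that assumption.

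**What to change.** 1. Reconcile the Days 2–4 procedure and Table 2 with the WRAT4 section, showing that one intervention visit has no WRAT-4.
2. State the expected number of exercise-rest academic pairs. State also that exercise versus TSST on this outcome is a between-child comparison adjusted for the rest WRAT-4 score.
3. Restate power for academic achievement on that number, or declare the assumption of an equal path b that lets both pair types be pooled.
4. For children not yet randomised, allocate 1:1, within each of the six orders, which of aerobic or TSST carries the WRAT-4.

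Items 1 to 3 are wording and a short calculation. Item 4 adds a column to the randomisation list and cannot reach children already tested; recruitment began in February 2019. The price is a less favourable power statement for one outcome domain. Securing 103 exercise-rest academic pairs by enlarging the trial would take 2 × 103 = 206 completers at an even split, or 206/(103/120) = 240 recruited at the plan's implied attrition, so restating the claim is the practical course.
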